Adequate wound healing/recovery following surgery (if applicable)	Contraindication to MRI or gadolinium
Able to provide study-specific written informed consent	Severe active comorbidity making patient unsuitable for radical RT and/or adjuvant chemotherapy
Able to complete baseline NCF testing in English	Any recognised genetic syndrome causing sensitivity to RT
Adequate haematological, renal and hepatic function for PCV chemotherapy	Contraindication to procarbazine, lomustine or vincristine, including coeliac disease and rare hereditary conditions of galactose intolerance, total lactase deficiency or glucosegalactose malabsorption
Able to swallow oral medication	Prior invasive malignancy, unless disease-free interval ≥3 years
Participants born female of childbearing potential must agree to be pregnancy screened prior to entering the trial, provide a negative pregnancy result within 7 days prior to randomisation and agree to use medically acceptable methods of contraception during RT, between the end of RT and start of adjuvant chemotherapy, during chemotherapy and for 6 months following the end of chemotherapy	Pregnancy or breastfeeding
Fertile participants born male must agree to use medically acceptable methods of contraception during RT, between the end of RT and start of adjuvant chemotherapy, during chemotherapy and for 6 months following the end of chemotherapy	Participant unable or unwilling to attend for follow-up
	Recognised genetic syndrome causing sensitivity to radiotherapy

IDHisocitrate dehydrogenaseKPSKarnofsky Performance StatusNCFneurocognitive functionODGoligodendrogliomaPCVprocarbazine, lomustine and vincristine chemotherapyRTradiotherapy

**Table 2 T2:** Schedule of assessments

	Baseline/pretreatment			Treatment	Post-RT follow-up							
	Eligibility/preregistration	Prerandomisation	Pre-RT	Weekly RT	1 month	3 months	6 months	1 year	2 years	3 years	4 years	5 years
Medical history	X											
Clinical assessment	X			X	X	X	X	X	X	X	X	X
Pregnancy test	X	X	X		X	X	X					
Informed consent	X											
MRI scan	X		X			X	X	X	X	X	X	X
Radiotherapy planning CT scan			X									
PBT or photon RT				X								
PCV chemotherapy						6×6-weekly cycles of adjuvant PCV chemotherapy						
Neurocognitive function tests*		X			X			X	X	X	X	X
CTCAE toxicity assessment		X		X	X	X	X	X	X	X	X	X
Endocrine assessments			X				X	X	X	X	X	X
HRQoL†		X		X‡	X	X	X	X	X	X	X	X
Work and economic impact§		X		X‡	X	X	X	X	X	X	X	X
Caregiver distress¶		X		X*‡	X	X	X	X	X	X	X	X

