#### Secondary endpoints

Secondary endpoints are shown in table 3.

**Table 3 T3:** Secondary endpoints

Endpoint	Definition/measurement
Additional NCF tests	Computer-based CNS Vital Signs platform, which evaluates attention, psychomotor speed, verbal/visual memory and aspects of executive functioning^44^
Caregiver distress	Caregiver needs screen
Work and economic impact (participants and carers)	WPAI: General Health Questionnaire, and Health Resource Use Questionnaire
Treatment compliance	Total dose of RT delivered; overall treatment time; details of any interruptions to RT and reasons; delivery of any fractions using photon RT instead of PBT; number of chemotherapy cycles; chemotherapy doses delivered; details of any modifications and reasons
Endocrinopathies	Static/dynamic testing of the following on blood samples: GH/IGF-1 FSH/LH Testosterone and SHBG (male participants) Oestradiol (female participants) Cortisol Free T3/T4, TSH Prolactin
Safety and toxicity	Acute (≤3 months post-RT) and late (>3 months post-RT) toxicities measured using CTCAE V.5.0.
HRQoL	EORTC QLQ-C30 and BN20, EQ-5D-5L, MFI and HADS.
Tumour response assessment	MRI brain performed with the following sequences: • T2 • FLAIR • DWI • T1 pregadolinium T1 postgadolinium Evaluation based on RANO criteria.
PFS	Time from randomisation to the date of the first-documented evidence of progression or death from any cause.
OS	Time from randomisation to the date of death from any cause.

CNScentral nervous systemCTCAECommon Terminology Criteria for Adverse EventsDWIdiffusion-weighted imagingEORTC QLQ-C30 and BN20European Organisation for Research and Treatment of Cancer Quality of Life Questionnaire and Brain Neoplasm QuestionnaireEQ-5D-5LEuroQol-5 Dimension-5 Response-Level QuestionnaireFLAIRfluid-attenuated inversion recoveryFSHfollicle stimulating hormoneGHgrowth hormoneHADSHospital Anxiety and Depression ScaleHRQoLhealth-related quality of lifeIGF-1insulin like growth factor 1LHleutinising hormoneMFIMultidimensional Fatigue AssessmentNCFneurocognitive functionOSoverall survivalPBTproton beam therapyPFSprogression-free survivalRANOresponse assessment in neuro-oncologyRTradiotherapySHBGsex hormone binding globulinTSHthyroid stimulating hormoneWPAIWork Productivity and Activity Impairment

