### Statistical considerations

#### Sample size

The primary endpoint of NCF at 5 years will be measured by calculating the mean of standardised z-scores from the HVLT-R, TMT-A/B and COWA components of CTB COMP. A Cohen’s d of 0.5 is regarded as a moderate effect size, which is considered to be clinically relevant given that even small deteriorations in NCF are likely to be impactful in this patient population.^22^ This CTB COMP score is also being used as the primary endpoint measure in the ongoing US NRG-BN005 trial of PBT versus photon RT for cognitive preservation in IDH mutant grade 2/3 glioma (Clinicaltrials.gov NCT03180502). Based on a two-sample t-test with 5% two-sided significance and 90% power, 172 participants (86 per arm) are required to detect an effect size of 0.5. Assuming 30% loss to follow-up at 5 years, 123 participants will be required per arm. The required sample size is therefore 246 participants, to be recruited over 3.5 years. The study is designed with an intermediate and final primary endpoint, whereby a significant positive treatment effect on either endpoint would warrant change in practice. Following the Food and Drug Administration (FDA) guidance on multiple endpoints in clinical trials, the family-wise error rate of 0.05 will be preserved using the fall-back method,^23^ with alpha of 0.01 allocated to the intermediate and 0.04 allocated to the final primary endpoint. Should a significant effect be observed on the intermediate endpoint, the full alpha of 0.05 will be used for the final primary endpoint analysis. Irrespective of the early interim assessment outcome, the trial will continue. Assuming the same sample size calculation, using a type I error of 0.04 (5 years) would provide ~89% power. At the 2 year time point, assuming a smaller dropout rate of 10%, a type I error of 0.01 would provide ~87% power.

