##### Secondary endpoints

Summary statistics by treatment arm at each timepoint will be presented for additional tests of NCF, HRQoL, caregiver distress, work and economic impact, treatment compliance, endocrinopathy and response assessment. Similar mixed-effects repeated measures models to those used for the primary endpoint will be used to compare HRQoL and additional NCF tests between treatment arms, adjusted for minimisation factors, relevant clinical characteristics and baseline HRQoL.

The numbers and proportions of participants experiencing each Common Terminology Criteria for Adverse Events (CTCAE) V.5.0 acute and late toxicity grade will be summarised.^27^ Safety data will be summarised using the safety population, with participants summarised according to the treatment they received. The proportion of participants experiencing serious adverse reactions and related unexpected serious adverse events will also be summarised.

Overall survival and progression-free survival will be analysed using Cox proportional hazards models. Kaplan-Meier and time to event estimates with 95% CIs will be presented.

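### Late toxicity, an open-ended outcome followed to 5 years, is summarised only as numbers and proportions; read as ever-experienced proportions over all treated participants, these would understate it under censoring

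*Protocol article*

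**What the plan says.** Table 3 of the Protocol article defines the safety endpoint as "Acute (≤3 months post-RT) and late (>3 months post-RT) toxicities measured using CTCAE V.5.0", so the late period has a start but no stated end. The row "CTCAE toxicity assessment" in Table 2 schedules visits before randomisation, weekly during RT, at 1, 3 and 6 months, and then yearly to 5 years.

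The Secondary endpoints text under Statistical analyses gives one summary for both periods: "The numbers and proportions of participants experiencing each Common Terminology Criteria for Adverse Events (CTCAE) V.5.0 acute and late toxicity grade will be summarised". It adds: "Safety data will be summarised using the safety population, with participants summarised according to the treatment they received". The preceding paragraph lists the outcomes to be summarised by arm at each timepoint, and toxicity is not among them. The following paragraph, on overall and progression-free survival, names Cox models and says: "Kaplan-Meier and time to event estimates with 95% CIs will be presented". No such method is named for toxicity.

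The Sample size section gives the expected attrition. At 5 years: "Assuming 30% loss to follow-up at 5 years, 123 participants will be required per arm". At 2 years: "assuming a smaller dropout rate of 10%, a type I error of 0.01 would provide ~87% power".

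**The concern.** For acute toxicity, a simple proportion over a window ending 3 months after RT is adequate, because few participants are lost that early. The late window runs to 5 years. A participant who leaves at year 3 without a late event has been observed for only part of it, yet an ever-experienced proportion over everyone treated counts that person as free of late toxicity to year 5. The proportion then falls below the 5-year risk that readers will take it to be.

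This matters because fewer long-term toxicities is the hypothesis for PBT in the Introduction, and the Discussion promises evidence on long-term toxicities of PBT compared with photon RT. Late CTCAE rates will be read in that light even though no formal test of them is planned.

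**Working it through.** **Step 1: the plan's own use of the 30%.** The Sample size section states: "Based on a two-sample t-test with 5% two-sided significance and 90% power, 172 participants (86 per arm) are required". A noncentral t calculation with d = 0.5 gives 86 per arm (power 90.3%). Allowing for loss, 86 / (1 − 0.30) = 122.9, rounded up to 123 per arm and 246 in total. The stated figures reproduce. The 30% enters the article only here, as an overall figure for the neurocognitive endpoint.

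**Step 2: inputs for the check.**
- Loss by 5 years, L = 0.30 (Sample size section), treated here entirely as censoring of participants who are alive.
- True 5-year risk of late toxicity, F: not given in the article, so assumed, over a range of 10% to 50%.
- Event and loss times independent, with constant hazards over 5 years. The 3-month start of the late period is ignored.
- Denominator: all treated participants.

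**Step 3: formula.** With h = −ln(1 − F)/5 and l = −ln(1 − L)/5,

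crude = h/(h + l) × [1 − exp(−5(h + l))] = h/(h + l) × [1 − (1 − F)(1 − L)].

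For F = L = 0.30, h = l = 0.0713, so crude = 0.5 × (1 − 0.7 × 0.7) = 0.255, or 25.5%.

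If events occur only in years 2 to 5, h₂ = −ln(1 − F)/3 and

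crude = exp(−2l) × h₂/(h₂ + l) × [1 − exp(−3(h₂ + l))].

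For F = L = 0.30, h₂ = 0.1189, so crude = 0.867 × 0.625 × 0.435 = 0.236, or 23.6%.

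| Assumed true 5-year risk | Crude, constant hazard | Crude, onset in years 2–5 |
|---|---|---|
| 10% | 8.4% | 7.8% |
| 20% | 16.9% | 15.7% |
| 30% | 25.5% | 23.6% |
| 40% | 34.2% | 31.5% |
| 50% | 42.9% | not run |

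The crude figure is about 84–86% of the true risk with constant hazard and about 78–79% with later onset.

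**Step 4: sensitivity to the pattern of loss.** With the article's own two points (10% lost by year 2, 30% by year 5) and a constant loss hazard within each period, the 30% risk appears as 26.0%, or 24.1% with later onset. The result does not hinge on evenly spread loss.

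**Step 5: sensitivity to deaths.** Death is a competing event: a participant who dies without late toxicity never has it, and counting that person as event-free is correct. As an illustration only, let half the loss hazard be death, d = 0.0357. The 5-year cumulative incidence is then h/(h + d) × [1 − exp(−5(h + d))] = 0.667 × (1 − 0.586) = 27.6%. The crude figure stays at 25.5%, so the shortfall is 2.1 points instead of 4.5. The article gives no split of the 30%.

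**Step 6: difference between arms.** With a true 30% in both arms and constant hazards, equal loss gives no spurious difference. Loss of 25% v 35% gives 26.3% v 24.7%, a gap of 1.6 points.

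**The case against.** The strongest objection is that the text fixes no denominator. Proportions among those assessed at each visit would also fit the sentence and would not be diluted in this way. The article also says that a detailed analysis document will be written, and denominators for descriptive safety tables commonly belong there. This stands as far as certainty goes: the understatement is conditional. It does not remove the point. Toxicity is left out of the list of outcomes summarised at each timepoint and has its own sentence, tied to the safety population, so the ever-experienced reading is the more natural one.

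The size is also open to challenge. The 30% was set for neurocognitive testing, part of it may be deaths, and the Data collection and management section provides for data from withdrawn participants where they allow it. All of this stands, so the calculated shortfalls are upper-end for the assumed risk.

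A reader might infer that follow-up alone will create a toxicity difference between the arms, since the trial is open-label and PBT involves travel. The documents do not support that. They state no unequal loss, travel concerns preassessment and treatment, and follow-up is at local sites for all participants. Loss of 20% v 40% would give a gap of 3.2 points (4.5 with later onset), but nothing in the article suggests such a split.

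Finally, if loss were related to toxicity, a cumulative incidence estimate with ordinary censoring would be biased too, and a first-event analysis does not show recovery or persistence. Both are reasons to add it to the counts, not to replace them.

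**Conclusion.** The point holds in conditional form. The only stated summary of late toxicity takes no account of incomplete follow-up. If it is an ever-experienced proportion over all treated participants, it will understate 5-year late toxicity to the extent that participants are censored alive and event-free. For an assumed true risk of 30% the shortfall is at most about 4.5 points with constant hazard, or 6.4 points with onset after year 2 (30% − 23.6%). It is smaller if some of the loss is death or if toxicity data continue after withdrawal. These sizes rest on an assumed toxicity rate and on non-informative loss. Bias between the arms is only a possibility. The toxicity summary is descriptive, and the primary analysis, alpha allocation and sample size are unaffected. This is a low-cost improvement to a secondary analysis.

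**What to change.** In the Secondary endpoints analysis text, keep numbers and proportions for acute toxicity. Keep them for late toxicity too, with the denominator stated (all treated, or those assessed at each visit). For late toxicity, add by treatment group the cumulative incidence of the first event at or above a prespecified grade, at 2 and 5 years with 95% CIs. Use the Aalen-Johansen estimator with death as a competing event and censoring at the last CTCAE assessment. Reporting the number still under assessment at each time by group would let readers see whether retention differs.

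The cost is some extra programming. The scheduled CTCAE visits already supply the timing, though with yearly visits onset may be known only to the interval between visits unless onset dates are recorded. The change can be made before any analysis and needs no additional visits.

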## Mechanistic component

It is hypothesised that there are definable RT dose–response relationships for specific structures/regions within the brain that are associated with impairments in NCF.^28^ Neurocognition is complex, and it relies on extensive, interconnecting networks of structures. The dose–response relationships for many of these regions and networks remain undefined.^28 29^ The APPROACH trial is an important opportunity to compare RT dosimetry with prospectively collected NCF data. Two approaches will be used as part of this work.

In the first approach, segmentation of the following structures will be performed on coregistered planning CT and MRI scans, based on existing atlases:^2330^,^33^ hippocampi (regions of neurogenesis and role in memory), temporal lobes (language, hearing and memory), cerebellum (attention, motor functioning), corpus callosum (processing speed), subventricular zones (neurogenesis), frontal white matter, anterior cingulate gyrus and frontal pole (executive functioning, memory, personality/behaviour and attention), precentral gyrus (primary motor cortex), occipital lobes (vision) and parietal lobes (sensation, spatial awareness). Dosimetric data will be exported from RT plans and corrected for fractionation to the equivalent dose in 2 Gy fractions (EQD2). These data will be compared with NCF data to identify relevant dose impairment thresholds for brain structures using methods similar to those used by Gondi *et al*, with consideration given to multiple hypothesis testing.^34^

In the second approach, lesion symptom mapping will be performed. This is a method for relating a specific region within the brain to a particular function and has been used in the setting of stroke and trauma.^35^ Similar to the method used by Habets *et al*, RT doses will be segmented on planning CT/MRI scans in dose bands in EQD2 and resection cavities/tumour will be segmented and subtracted to produce a map of normal tissue doses.^36^ Individual normal tissue dose location maps (DLM) will be registered to a standard 3D brain template and grouped together to create probability maps for the presence of dose in each voxel. For each neurocognitive domain and each dose band, we will compare DLMs at voxel level between participants with and without neurocognitive impairment at 5 years, with consideration of multiple hypothesis testing.

The mechanistic component may identify particularly sensitive brain subregions and/or interconnecting neural networks, the dose to which could be constrained during RT planning. It could also highlight scenarios where the normal tissue sparing properties of PBT would be particularly helpful. Where normal tissue doses to particular brain regions cannot be minimised, for example due to tumour location, improved understanding of relationships between RT dosimetry and impairment of NCF may permit more informed discussions regarding potential benefits and risks of treatment. It could also inform strategies to provide targeted neurorehabilitation of specific RT-related neurocognitive toxicities.

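### The voxel-level dose mapping reduces continuous NCF scores to impaired or not impaired; the continuous score should carry the main map, with the impairment map as secondary

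*Protocol article*

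**What the plan says.** The second approach in the Mechanistic component is lesion symptom mapping. On the dose side, "RT doses will be segmented on planning CT/MRI scans in dose bands in EQD2", tumour and cavity are removed, and the individual maps are combined to "create probability maps for the presence of dose in each voxel". On the outcome side, participants are divided in two: "we will compare DLMs at voxel level between participants with and without neurocognitive impairment at 5 years". The comparison is repeated "For each neurocognitive domain and each dose band", and is to be made "with consideration of multiple hypothesis testing".

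Elsewhere NCF stays continuous. The Sample size section defines the 5-year endpoint by "calculating the mean of standardised z-scores from the HVLT-R, TMT-A/B and COWA components of CTB COMP". The Primary endpoint section (Statistical analyses) compares mean scores with a mixed model, and the Secondary endpoints section plans similar models for the additional NCF tests.

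The article states no sample size or power for the voxel analysis. It gives no impairment cut-off, expected prevalence of impairment, band limits, voxel-level test or voxel-level alpha. An article may leave these to the full protocol or analysis plan, and their absence is no part of this point. The division of participants by impairment status is stated, and that is the point.

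**The concern.** Once scores are cut, a participant just on the unimpaired side counts the same as one with an excellent score, and one just on the impaired side counts the same as one who is profoundly impaired. The distances between participants, which a dose-response analysis needs, are lost.

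The component aims to find sensitive subregions whose dose could be constrained in planning. The number of participants with 5-year scores is fixed by the primary endpoint, and the voxel tests must also bear a multiplicity correction. Information given up at the outcome cannot be recovered later, so a truly dose-sensitive region is more likely to go undetected.

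**Working it through.** **1. Inputs from the article (Sample size section).** The calculation is a t-test at a two-sided 5% level, aiming for 90% power. Its result is that "172 participants (86 per arm) are required to detect an effect size of 0.5". With 30% loss to follow-up, 86 / 0.7 = 122.9, so 123 per arm and 246 in total.

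**2. The plan's own figure.** Two-sample t-test, 86 per arm, d = 0.5, two-sided alpha 0.05: noncentrality = 0.5 × √(86 × 86 / 172) = 3.28 on 170 degrees of freedom, giving power 0.903. The stated 90% is reproduced.

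**3. Assumptions.** None of these is in the article for the voxel analysis:
- 172 participants contribute (the primary endpoint's evaluable number);
- scores are normal and shifted down by d in participants dosed at the voxel;
- impairment prevalence p is 10% to 50%;
- the share dosed, d and alpha are as given in each step below.

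The d = 0.5 in step 5 is borrowed from the comparison of treatment arms purely as a reference size.

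**4. Information kept by the outcome cut.** For small effects, the efficiency of the cut outcome relative to the full score is φ(z_p)² / [p(1 − p)], where z_p is the normal quantile of p and φ the normal density. It does not depend on the share dosed or on alpha.

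| Impaired | φ(z_p) | Efficiency | 172 participants count as about |
|---|---|---|---|
| 50% | 0.399 | 0.64 | 109 |
| 30% | 0.348 | 0.58 | 99 |
| 20% | 0.280 | 0.49 | 84 |
| 10% | 0.175 | 0.34 | 59 |

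**5. Illustration in power.** d = 0.5, half dosed (86 and 86), two-sided alpha 0.05. The t-test on the score has 90% power, as in step 2. For the cut outcome, the threshold is set so that overall prevalence is p. With p1 and p0 the proportions impaired among dosed and undosed participants, power = Φ[(p1 − p0 − 1.96 s0) / s1], where s0 = √[2p(1 − p)/86] and s1 = √{[p1(1 − p1) + p0(1 − p0)]/86}.

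Example, p = 20%: p1 = 0.268, p0 = 0.132, s0 = 0.0610, s1 = 0.0601; (0.1364 − 0.1196) / 0.0601 = 0.28; power 61%.

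| Impaired | p1 | p0 | Power, cut outcome | Loss from 90% (points) |
|---|---|---|---|---|
| 50% | 0.599 | 0.401 | 74% | 16 |
| 30% | 0.385 | 0.215 | 69% | 21 |
| 20% | 0.268 | 0.132 | 61% | 29 |
| 10% | 0.142 | 0.058 | 45% | 45 |

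Simulation with a chi-square test gives losses of 14 to 46 points over the same range.

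**6. How far the loss moves with the assumptions.**
- *Near the ceiling:* d = 0.8, alpha 0.05, 30% to 50% dosed, 30% to 50% impaired. Full-scale power is above 99% and the loss is about 1 to 4 points.
- *Near zero:* d = 0.5, alpha 0.00001, 30% dosed. Power is about 7% with the score and 1% to 2% after the cut. Both analyses fail.
- *Stricter alpha with a larger effect:* d = 0.7, alpha 0.001, 30% dosed. Power is 80% with the score, against about 49%, 51%, 45% and 31% at 50%, 30%, 20% and 10% impaired.

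**The case against.** **The size is not anchored in the article.** This stands. The power losses need a prevalence, a share dosed, a voxel effect and an alpha that the article does not give. A reader might take 16 to 45 points as the general cost; step 6 shows that it is not. Nominal 0.05 is also an unlikely voxel-level alpha once multiplicity is handled. The efficiency figures need fewer inputs, but still rest on the normal shift, which favours the continuous test, and on prevalence.

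**Impairment is part of the question.** This stands in part. The Mechanistic component speaks of impairments in NCF, and its first approach looks for dose thresholds for impairment. That justifies keeping an impairment map. It does not justify making it the only voxel-level comparison, since the stated hypothesis concerns dose-response relationships.

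**Stronger readings that the text does not support:**
- Each voxel test may look like a 2×2 table, but no test is named.
- Similarity to an earlier study may look like the only reason for the impairment cut, but that remark is attached to the segmentation and subtraction of dose.
- Banding the dose may look as costly as cutting the outcome, but several bands keep more information than a single cut, and the number and limits of the bands are not given. No size is claimed for it here.
- A null map might be misread as showing that a region tolerates dose, but nothing in the article says that it would be read that way.

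**The component is exploratory.** This stands. It is one of two mechanistic approaches.

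**Conclusion.** The point holds, centred on the outcome cut. The article commits the voxel mapping to a yes/no outcome although a continuous score is available. Under a normal shift, this keeps about 64% of the information at best (half impaired) and about 34% at 10% impaired. In the reference scenario, power of 90% becomes about 74% to 45%. These figures rest on assumed inputs, and the loss shrinks to a few points when full-scale power is near its ceiling or near zero.

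A reader might infer that the trial's main result is weakened. It is not: the primary endpoint stays continuous, and the sample size and its power are untouched. This is a cheap improvement to an exploratory component.

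**What to change.** For each domain, make a voxel-wise model with the participant's continuous 5-year NCF z-score as outcome the main mapping analysis, under the multiplicity control already planned. Either enter voxel EQD2 as a continuous predictor, which also removes the need for a separate test per dose band, or keep the bands and compare z-scores between participants with and without dose in the voxel. Keep the impaired/not-impaired map as a secondary analysis, because the component also asks about impairment.

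The cost is analysis-plan wording. Scores and dose maps are collected anyway, and no participants, visits or imaging are added. The downside is that the main map shows a difference in z-score rather than impairment, and is less directly comparable with the earlier study whose mapping method is followed; the secondary map covers both.
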